## Abstract

**Trial registration:**

ClinicalTrials.gov CTRI/2024/08/072748.

## Introduction

Non-communicable diseases (NCDs) are the leading causes of morbidity and mortality globally, accounting for nearly two-thirds of deaths. In India, NCDs account for 16,939 disability-adjusted life years (DALYs) per 100,000 population, alongside high out-of-pocket and catastrophic health expenditures [1]. The co-occurrences of NCDs and, mental and substance use disorders (MSUDs) significantly impact treatment adherence and health outcomes. Multimorbidity of physical and MSUDs has been previously described as a ‘rule’ [2].

MSUDs, including depression, anxiety, alcohol use disorders, and tobacco use disorders, contribute substantially to this burden, often co-occurring with chronic conditions like cardiovascular diseases and diabetes [3]. For instance, individuals with alcohol misuse have a 1.4 times higher likelihood of developing heart disease, while anxiety disorders increase this risk to 2.2 times [4]. Moreover, persons with MSUDs are at a higher risk of living with the risk factors for NCDs, including an unhealthy diet and physical inactivity. Common biological mechanisms like immune and inflammatory pathways to shared social determinants (e.g., poverty) could explain the co-occurrence of mental disorders and other NCDs [2].

Studies indicate that the co-existence of NCDs, such as hypertension and diabetes, with depression and other mental disorders is detrimental to care and prognosis, leading to poor glycaemic control, uncontrolled hypertension, greater risk of cardiovascular complications, and higher mortality rates [5]. As per the United Nations Development Programme, of the estimated 15 million excess deaths over 2020–2021, a significant portion were likely to be people living with NCDs. A survey conducted by the World Health Organization (WHO) across 60 countries found that 9.3–23% of patients with chronic diseases had comorbid depression [6]. Moreover, NCDs affect one’s mental well-being and functioning, impacting treatment adherence, and MSUDs are risk factors for NCDs. There is a need for immediate, focused attention to both MSUDs and NCDs [7,8]. Scaled-up investment for mental health and other NCDs is crucial. In addition, integration of care for MSUDs, in NCD care is the need of the hour.

In 2017, NCDs constituted 46.6% of national DALYs, with neuropsychiatric conditions among the top five contributors to disability [9]. Studies indicate that comorbidities such as hypertension and diabetes, when coupled with depression, worsen prognosis and increase mortality risks [10,11]. However, MSUDs services in the country are hindered by systemic barriers at various levels, including service provider factors [12], cultural factors, and sociopolitical factors [13].

Mental health programmes and activities in the country have been described as fragmented and disorganized and have a low priority during implementation, as they suffer from administrative, technical, and resource constraints and, thus, result in limited reach [14]. The poor infrastructure and shortage of human resources of the health care system for the treatment of mental disorders have also been documented previously [15]. Despite initiatives like the National Programme for Prevention & Control of Non-Communicable Diseases (NP-NCD) in India, the integration of mental health into NCD care remains inadequate due to systemic barriers such as cultural stigma, geographic constraints, and insufficient infrastructure and trained human resources [16,17]. Currently, India has only two mental health workers and 0.75 psychiatrists per 100,000 population, which is below global average [18]. The treatment gap for mental disorders ranges from 70% to 92%, underscoring the urgent need for integrated healthcare approaches that effectively address both NCDs and mental health [19]. To address these treatment gaps in mental health care in India, a critical research question arises: How can mental health care be effectively integrated into the existing healthcare framework?

While the moment is opportune to integrate mental health care delivery into the NCD care delivery at various levels of health care delivery, the health system needs to be prepared for the proposed integration. The lessons from the NP-NCD and the National Mental Health Programme of India offer valuable resources to plan and implement the proposed integration.

Comprehensive Primary Health Care (CPHC) aimed to provide health services to communities, and the Ayushman Bharat (AB) program was launched to strengthen CPHC services. One of the key components of the AB program is to enable the expansion of the package of services that go beyond maternal and child health to include care for non-communicable diseases, palliative and rehabilitative care, oral, eye, and ENT care, mental health, and first-level care for emergencies and trauma.

While there has been a growing focus on the common behavioural risk factors, including tobacco use, alcohol use, and unaddressed psychosocial stress, evidence-to-practice gaps exist at various levels of implementation, including segregated management protocols, low data quality and reporting, weak supply chains, and low treatment adherence. Also, to ensure a successful integration, the mental health component of CPHC needs to focus on simplifying disorder-related concepts into elements that the health workers can easily and quickly understand; integration of the mental health component into the practicing style of the health workers so that they can pick up mental health issues during their routine practice; task-shifting; using affordable and straightforward technology; and facilitation of promotion of universal prevention-focused interventions common to both mental disorders and other NCDs [20].

Hence, there is a need to plan the integration meticulously to reach the desired goal. This requires structured implementation of the proposed integration using the building blocks of a health system comprising of service delivery, health workforce, health information system, medical products, financing, leadership, and governance [21]. Such a framework would address the gaps in all the tiers of a health system, starting from a sub-center to a tertiary referral health facility. Moreover, the process of proposed integration needs to be studied systematically.

### Aims & objectives

The aims of the study are to develop, assess the feasibility, implement a service delivery model to achieve high coverage (≥70%) of screening, management, and linkage to care of common mental disorders (CMDs) and substance use disorders (SUDs) among individuals seeking care for non-communicable diseases (NCDs) at public health facilities and to evaluate the cost associated with the implementation of the proposed service delivery model.

The primary objective is to develop and implement a service delivery model that would result in high coverage (at least 70%) of screening, management, and linkage to care of common MSUDs among persons seeking care for NCDs at public health facilities. The secondary objectives are to (a) assess the feasibility of adoption of the implementation model by the health care system and (b) evaluate the costs of the mental health service strengthening intervention package from the health system as well as the patient’s perspective.

## Materials and methods

### Study design

It is a multi-site implementation research study employing a mixed-methods, single-arm, quasi-experimental interrupted time series design with a pre-post approach conducted within-site over three phases and without a control group. The study would incorporate formative and evaluative components into iterative improvement cycles.

### Study setting

The study will be carried out in seven states across India. The states are self-governing administrative divisions, and each of them has a state government. The governing powers of the states are shared among the state government and the union government. The study in each state shall be overseen by investigators belonging to a local medical institution having a medical school and an attached tertiary care hospital. These states and the institutions offering the oversight include Assam [All India Institute of Medical Sciences (AIIMS), Guwahati], Madhya Pradesh (AIIMS, Bhopal), Gujarat (Gujarat Institute of Mental Health, Ahmedabad, Gujarat), Haryana (AIIMS, New Delhi), Karnataka (St. John’s Medical College Hospital, Bengaluru), Odisha (AIIMS, Bhubaneswar), and Punjab [Post Graduate Institute of Medical Education and Research (PGIMER), Chandigarh].

Within each state, one district has been selected for the study. These include Kamrup (Assam), Vidisha (Madhya Pradesh), Gandhinagar (Gujarat), Faridabad (Haryana), Bengaluru-Rural (Karnataka), Khordha (Odisha), and Mohali (Punjab). These districts have been identified in each of the states in consultation with the respective state health department. Intervention will be implemented at all the health facilities in the district. However, evaluation will be done at 81 health facilities in each district. In total, 567 health facilities will be evaluated to assess the implementation outcome, patient outcome, and service outcome. The public health care delivery systems at all levels of care delivery, including Ayushman Arogya Mandirs, sub-centers, Primary Health Centers (PHCs), Community Health Centers (CHCs), District Hospitals, and tertiary care hospitals in rural and urban areas (depending on the need and feasibility), shall be included in the study. The coordinating site would be the Indian Council for Medical Research (ICMR), Headquarters (HQ), New Delhi. The estimated time of completion of data collection will be October 2026, and the results are expected in January 2027.

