In **Phase III**, the final model shall be implemented across the district at each of the sites. The primary evaluation outcome is facility-level coverage of the mental health screening and management strategy. We require an estimate of coverage of 70% with an absolute precision of ±10% and 95% confidence. Using the single-proportion formula n = Z^2^ p (1 − p)/ d^2^, with Z = 1.96, p = 0.70, and d = 0.10, gives n = 80.7, rounded up to 81 health facilities per district. The implementation cascade was designed such that screening, referral, and management rates of ≈90% at each step yield an overall coverage of 0.9 × 0.9 × 0.9 = 0.729 (≈72.9%), which is slightly conservative with respect to the 70% target. Because the primary unit of analysis is the facility, this sample-size calculation does not require an intra-cluster correlation correction; however, if analyses are to be performed at the individual level or if clustering is a concern, the sample will be inflated by an appropriate design effect (DEFF = 1+ (m − 1) ρ), and allowance will be made for anticipated non-response. A sensitivity analysis using DEFF values between 1.2 and 1.5 and a 10% non-response adjustment is presented in Supporting Information S1 Table. (S1 Table – Sensitivity Table using Appropriate Design Effect)

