### Sampling method

We will be using a multistage sampling approach that will be adopted to ensure representation across multiple stakeholder groups and healthcare delivery levels. Initially, the seven states were selected by the expression of interest, and later districts were selected after the discussions with the respective states.

In **Phase 1**, purposive sampling will be used to recruit key informants, including policymakers, administrators, healthcare workers, community representatives, and patients, to capture diverse perspectives on mental health integration.

In **Phase 2** and **Phase 3**, all healthcare facilities—Ayushman Arogya Mandirs (AAMs), Sub-centres (SCs), Primary Health Centres (PHCs), Community Health Centres (CHCs), and District Hospitals (DH)—as well as all health cadres involved in mental health service delivery under the District Mental Health Programme (DMHP), including Medical Officers (MOs), Community Health Officers (CHOs), and Accredited Social Health Activists (ASHAs), will be included.

This staged approach allows for systematic recruitment from broader administrative and policy levels down to frontline providers and end-users, facilitating comprehensive data collection across the health system. A flowchart of the multistage sampling method is presented in Fig 1.

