#### Phase-2 – model optimization.

In Phase-2, based on the insights gained from pilot testing, subsequent iterations of the model (e.g., M1, M2…Mx) will be developed to improve coverage and quality of MSUD services. Each iteration will incorporate lessons learned from previous cycles, such as adjustments to training content, improvements to digital tracking tools, and enhanced patient engagement strategies. These iterative cycles will continue until a model is identified that demonstrates high coverage, feasibility, and effectiveness across all levels of the healthcare system.

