#### Phase-3-full implementation and evaluation.

The optimized implementation model finalized in Phase II shall be implemented across all the healthcare facilities across all the selected districts. We will continue to use the nine aspects of concept mapping as suggested in the Expert Recommendations for Implementing Change (ERIC) [34] while implementing the optimized model across the selected Taluks or the whole district.

The implementation support team (the research team) will continue to be active in the capacity of facilitator and advisor to the implementation teams (HCWs engaged in care delivery). There will be ongoing mentorship and quality improvement feedback cycles within each facility. Implementation activities will include ensuring access to and use of the intervention package, the digital platform, and the application; HCW training; community awareness and demand generation; establishment of referral and supervision systems; monitoring; and continuous feedback loops.

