Recruitment	Procedures used to approach and attract participants at individual or organizational levels; includes maintenance of participant involvement in intervention and measurement components of study.	Monitor and document recruitment procedures to ensure protocol is followed; adjust as needed to ensure reach.	• Recruitment of the Health care workers for the training will be based on the list provided by the District Health Officer. • Persons aged 18 years and above, being screened for NCDs or diagnosed with NCD	• Number of requests placed with district administration for training of ANM/ ASHA/ CHO/ MO • Proportion of ANM/ ASHA invited to participate in the training sessions • Proportion of CHO invited to participate in the training sessions • Proportion of MO invited to participate in the training sessions • Proportion of ANM/ ASHA contacted telephonically/ personally to ensure participation in the training programs • Proportion of CHO contacted telephonically/ personally to ensure participation in the training programs Proportion of MO contacted telephonically/ personally to ensure participation in the training programs
Context	Aspects of the environment that may influence intervention implementation or study outcomes; includes contamination or the extent to which the control group was exposed to the program.	To monitor aspects of the physical, social, and political environment and how they impact implementation and needed corrective action.	• The environmental aspects which can affect the service delivery implementation or outcomes will be ascertained during the formative research and then the solutions would be obtained during the model optimizations and then the intervention will be delivered • Also to prevent contamination, each phase of the study would be done in only one or two blocks/wards	• Number of additional trainings on MSUD carried out in the district besides the training as part of the Project ICMR • Organization that conducted the training • Details of the content, duration, venue (online/ offline), trainers for the training (psychiatrist/ psychologist/ others) disorders covered, type of interventions converted (screening, assessment, management, referral, etc.) for training • Number of the HCWs (ANM, ASHA, CHO, MO) from the block included in the phase II who attended the training

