13. Does the district hospital have at least one medicine to treat alcohol use disorder (short term)?
14. Does the district hospital have at least one medicine to treat alcohol use disorder (long-term)?
15. Does the district hospital have at least one medicine to treat tobacco use disorder?
16. Proportion of PHC that have routine blood tests (LFT, KFT)
17. Proportion of CHC that have routine blood tests (LFT, KFT)
18. Does the district hospital have routine blood tests (LFT, KFT)?
19. Proportion of health facilities that have IEC material on MSUD available and displayed
20. Number of mental health awareness sessions held (at facility/in community)

The process of implementation will be evaluated by the COM-B model of the Behavior Change Wheel (BCW) [35]. As per this model, there are 3 key factors & multiple sub-factors capable of changing behavior, namely capability, opportunity, and motivation.

Program learning shall be documented using the qualitative methods (FGD, IDI), including listing barriers and facilitators, reasons for not following through with treatment, follow-up consultations (provider plus beneficiary), feasibility and acceptability of the training module/program through questionnaires and FGDs, technical and logistical challenges in delivering the program, challenges faced by staff during the completion of the course and their subsequent engagement (reaching out and referring), difficulties encountered when participating in the online refresher training, and the overall satisfaction level of staff post-training.

The timeline for all the study-related activities is provided in the Gantt chart (Table 10).

**Table 10 pone.0332359.t010:** Gantt Chart of the ICMR MINDS.

Project Activities		2024		2025		2025		2026		2026		2027	
		**Q 1**	**Q 2**	**Q 3**	**Q 4**	**Q1**	**Q2**	**Q3**	**Q4**	**Q1**	**Q2**	**Q3**	**Q4**
**1.1**	**Ethical clearance**												
**1.2**	**Registration of trial with CTRI**												
**2.1**	**Formative Phase**												
**2.2**	**Implement Initial MD in NCD Integration Model-0 in Block 1.**												
**2.3**	**Implement modified MD in NCD Integration Model-1 in Block 2.**												
**2.4**	**Implement modified MD in NCD Integration Model-X in Block.**												
**2.5**	**Program Learning Activities**												
**3.1**	**Implement the best model of MD in NCD Integration of Model-X in 2/3 new blocks.**												
**3.2**	**Process-monitoring activities**												

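### Phase III is given incompatible footprints, some too small for 81 facilities per district, and the blocks where the model is tuned are not separated from the evaluation

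*Protocol article*

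**What the plan says.** Several sections of the protocol article make Phase III district-wide:

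- Study setting: "Intervention will be implemented at all the health facilities in the district. However, evaluation will be done at 81 health facilities in each district".
- Sample size: "the final model shall be implemented across the district at each of the sites".
- Sampling method: Phases 2 and 3 both take in every public facility type from Ayushman Arogya Mandirs (AAMs) up to district hospitals, without restriction.
- Phase 3 section, opening sentence: the optimised model "shall be implemented across all the healthcare facilities across all the selected districts".

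Others make it narrower or leave it open:

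- Phase 3 section, next sentence: "while implementing the optimized model across the selected Taluks or the whole district".
- Table 10 (Gantt chart), row 3.1: "Implement the best model of MD in NCD Integration of Model-X in 2/3 new blocks".
- Table 6, Context row: "to prevent contamination, each phase of the study would be done in only one or two blocks/wards".
- Discussion, limitations: the research is described as restricted to some blocks of a district.

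On development, the Sample size section has the model refined in the Phase I block or ward. Gantt rows 2.2–2.4 name Block 1, Block 2 and a further block. The Phase 2 section gives the stopping rule: "These iterative cycles will continue until a model is identified that demonstrates high coverage", together with feasibility and effectiveness. Only Gantt row 3.1 describes the Phase III blocks as new.

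**The concern.** Two things depend on the footprint. The first is whether the planned sample exists. The 81 facilities per district come from a precision formula, and nothing in the article checks that number against the facilities available in one, two or three blocks.

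The second is what the coverage estimate means. Coverage is the primary evaluation outcome, and it is also the quantity on which development stops. The development block has a model fitted to its own staff and workflows, and longer exposure to training and support. If such facilities are among the 81, the result mixes performance where the model was built with performance where it was rolled out. A reader who wants to know what the final model does in fresh blocks, which is the question for scale-up, cannot separate the two.

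**Working it through.** **1. The plan's own figure.** Sample size section: Z = 1.96, p = 0.70, d = 0.10.
n = Z²p(1 − p)/d² = 1.96² × 0.70 × 0.30 / 0.10² = 80.67, rounded up to 81. Over seven districts, 81 × 7 = 567. Both figures reproduce.

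**2. Facilities per block.** The Sample size section expects one CHC, 3–6 PHCs and 5–6 AAMs per PHC in each block. Facilities = 1 + PHCs + PHCs × AAMs per PHC.

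| PHCs | 5 AAMs per PHC | 6 AAMs per PHC |
|---|---|---|
| 3 | 19 | 22 |
| 4 | 25 | 29 |
| 5 | 31 | 36 |
| 6 | 37 | 43 |

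This excludes separate sub-centres, for which no count is given, and the district hospital.

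**3. Does 81 fit?**

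| Footprint | Facilities | Block size needed for 81 | Cells of the table above that reach it |
|---|---|---|---|
| One block | 19–43 | 81 | 0 of 8 |
| Two blocks | 38–86 | 40.5 | 1 of 8 |
| Three blocks | 57–129 | 27 | 5 of 8 |

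Put the other way, 81 facilities correspond to 81/43 = 1.9 up to 81/19 = 4.3 blocks. Adding the one district hospital lowers the required block size to 80/2 = 40 and 80/3 = 26.7, which changes none of the cell counts.

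**4. Precision at the smaller numbers.** By the article's formula, d = 1.96 × √(0.21/n):

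- n = 81: ±10.0 points
- n = 57 (three small blocks): ±11.9
- n = 43 (one large block): ±13.7
- n = 38 (two small blocks): ±14.6
- n = 19 (one small block): ±20.6

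These treat the facilities as a sample from a larger population. If every facility in a small footprint is evaluated and inference is confined to that footprint, a finite-population correction applies.

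**5. Possible shift from development facilities.** Let w be the share of the 81 that lie in development blocks and Δ the excess coverage there over new blocks. Overall coverage minus new-block coverage = w × Δ. The article gives neither quantity, so the values of Δ and the number of blocks are assumptions.

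| Make-up of the 81 | w | Δ = 5 points | Δ = 10 points | Δ = 20 points |
|---|---|---|---|---|
| Development block omitted | 0 | 0 | 0 | 0 |
| Proportional draw, one of 3–10 equal blocks | 0.10–0.33 | 0.5–1.7 | 1.0–3.3 | 2.0–6.7 |
| Whole development block included (19/81 to 43/81) | 0.23–0.53 | 1.2–2.7 | 2.3–5.3 | 4.7–10.6 |

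If two blocks are used for development, as Gantt rows 2.2 and 2.3 suggest, the proportional shares double, to 0.20–0.67.

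**The case against.** The district-wide statement appears in the setting, sample-size, sampling and Phase 3 sections, which are the natural places to fix the design. The Gantt row and the Table 6 entry might be leftovers, and the Table 6 entry might be meant for the development phases. Under the district-wide footprint nothing shows that 81 facilities are lacking. That is fair, but Table 6 refers to each phase, the limitations paragraph also speaks of blocks, and the Phase 3 section leaves the choice open in its second sentence. The contradiction stands.

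The objection to any claim of bias is stronger. A reader might infer that the coverage result is biased upward. The documents do not show this. District-wide describes where the model is implemented, coverage is measured only in the 81, and the article does not say whether these include a development block. How the 81 are chosen could properly be left to a fuller document. If the target is average district coverage, which fits the stated objective, development facilities belong in it and including them is not a bias. The possible bias is therefore conditional: it exists only if development facilities are evaluated and the question is performance elsewhere.

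A reader might also set the possible shift against the gap between 72.9% and 70% in the Sample size section and conclude that a finding of success could be overturned. That is not supported. The 72.9% is the product of three 90% cascade steps, offered as design rationale. The study is sized to estimate coverage within ±10 points, and no test against 70% is stated. Against ±10 points, a shift of 1–3 points is modest.

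**Conclusion.** The contradiction in Phase III scope is established from the text alone. It has a practical consequence: with 19–43 facilities per block, 81 per district cannot come from one block, comes from two only at the top of the range, and comes from three over part of it. This rests on the article's expected counts and excludes separate sub-centres, which could raise the numbers.

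The effect on measured coverage is a possibility of unknown size, not a demonstrated bias. It is zero if the 81 omit the development blocks. It is about 1–3 points under a proportional draw with one development block among 3–10 equal blocks and an assumed 10-point excess, and larger if more development facilities are included or the excess is greater. The upward direction is plausible because development stops on the same outcome and exposure there is longer.

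It would go too far to conclude that development blocks must be removed from the primary estimate. They can belong to a district-wide target, and removing one block from a three-block district leaves only 38–86 facilities.

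**What to change.** 1. State one Phase III footprint and use it in Study setting, Sample size, Sampling method, the Phase 3 section, Table 6, Table 10 and the limitations. State also which blocks are used for development, since the Sample size section and the Gantt chart differ.
2. If the footprint is fewer blocks than the district, restate the number of facilities available and the precision they give, with a finite-population correction where all of them are evaluated.
3. Draw the 81 by random sampling, stratified by facility type and by development versus new block.
4. Report coverage separately for development and new blocks, with the new-block estimate beside the overall figure.

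The cost is wording, a sampling list and one extra line in the results; no facilities are added. The downside is a somewhat wider interval for the new-block estimate. With one of 3–10 equal blocks used for development and a proportional draw, 81 × 2/3 = 54 to 81 × 9/10 ≈ 73 facilities remain. By the formula above that gives about ±12.2 to ±10.5 points instead of ±10.
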